Early detection and diagnosis of declining cognition may not only allow health care providers (HCPs) to intervene in cases where the condition is reversible but also provide early and optimal management, tailored treatment planning, and timely access to education and psychosocial support to those at high risk for dementia [25-27]. However, screening for MCI in asymptomatic people 65 years and older is not recommended in Canada [9,28,29] or the United States [30,31]; case finding is the favored approach [32]. This is partly because of the limited availability of randomized controlled trials and clinical heterogeneity, which impedes our ability to generalize what may be small-to-moderate short-term improvements in cognitive function through early interventions such as exercise and cognitive training or pharmacotherapies [33-39]. Furthermore, dementia is a syndrome, not a disease [6,40,41], where the indicators are continuous and affected by a wide variety of factors such as education and genetics, and thus require expert clinical judgment for a definitive diagnosis [40,42]. Diagnosis is difficult because HCPs rely in part on patients to self-identify or informants to report symptoms of cognitive dysfunction [25]. In Canada, it is estimated that up to 10% of community populations aged 65 years and older have some form of undetected cognitive impairment [35], and in the United States, up to 76% of those who have experienced confusion or memory loss do not consult a health care professional [43]. Consequently, only 20%-50% of people with dementia are recognized and documented in primary care [44]. Asymptomatic screening is not recommended [45], and some believe that MCI screening may generally cause anxiety (although there is no supporting evidence [46]) and possible overtreatment of patients who are unlikely to develop dementia [22].

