### Study Participants and Recruitment

#### Patients

Patients 55 years and older with no history of diagnoses for MCI, dementia, or Alzheimer disease rostered in one of the FHTs participating in the study will be eligible to participate. The age of eligibility includes those 55 years and older to capture an at-risk population with no current diagnosis of MCI who might be healthy or experiencing early symptoms of MCI that may or may not be apparent to the participant. Prospective participants may also be excluded based on a diagnosis with any of the following conditions that are associated with MCI or dementia-like symptoms (Textbox 1): major depression requiring hospitalization, psychiatric disorders (ie, schizophrenia and bipolar disorder), psychopathologies, epilepsy, substance use disorders, and sleep apnea (without the use of a continuous positive airway pressure machine [77]). These criteria have been used in similar MCI screen validation studies to exclude participants that may confound the interpretation of the screen results because they are experiencing symptoms of MCI or dementia, not because of the true presence of MCI but rather unrelated conditions. The use of tablets to complete the SCREEN requires that participants are able to read and think in English, discern color, and read 12-point font on the tablet and that they have adequate hearing and vision to interact with the administering HCP and adequate hand and arm function to manipulate and hold the tablet. Exclusion criteria, therefore, include colorblindness or any disability that impairs a person’s ability to hold and interact digitally with the tablet. Finally, patients must be available to participate in a minimum of 2 screenings, performed 3 months apart, and an entry and exit interview to participate in the study. Prospective participants will be required to be rostered with 1 of the 5 participating FHTs to ensure that HCPs can access their electronic medical record (EMR) and that there was a physician responsible for follow-up referral. Before study enrollment, HCPs will be required to screen their EMR to verify participant eligibility and, on an ongoing basis, update their EMR with the results of the MCI screens.

Eligibility criteria for patient participants.

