#### The Qmci Screen

The Qmci is a sensitive and specific screen that differentiates normal cognition from MCI [63,65]. The HCP will administer the screen by asking the patient questions and recording their response on a dedicated Qmci assessment form provided by the screen developers. The patient will be required to answer 1 question via paper and pencil. The Qmci takes approximately 5 minutes to complete, is scored by hand out of 100 points, and evaluates 6 cognitive domains: orientation (10 points), registration (5 points), clock drawing (15 points), delayed recall (20 points), verbal fluency (20 points), and logical memory (30 points) [68]. The overall cut-off score to distinguish normal cognition from MCI on the Qmci is ≤67, from cognitive impairment (MCI or dementia) ≤62, and dementia alone ≤54 [88]. Although not as broadly adopted as the MoCA 8.1 in Canada, its psychometric properties, administration time, and availability for use suggest that Qmci is the optimal market assessment tool for MCI screening in FHT settings.

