To determine the sensitivity and specificity of the SCREEN in comparison with the Qmci, the results of both screens will be classified in binary format as healthy or not healthy, where *healthy* denotes SCREEN=no areas of challenge in all 7 activities and Qmci≥67 and *unhealthy* denotes SCREEN=1 or more areas of challenge and Qmci≤67. Consistent with consensus guidelines for screening for cognitive impairment [37,49,50], the research protocol will also require HCPs to refer patients to their primary care physician for further evaluation if they receive an abnormal score on the Qmci or significant concerns on the SCREEN. The SCREEN does not have a standardized cut-off score that can be used to classify results as abnormal. Therefore, in consultation with and on the recommendation of the SCREEN developers, for the purpose of the research protocol, a set of cut-off scores was developed to classify SCREEN results as normal (zero areas of challenge), some concerns (≤3 areas of challenge), or significant concerns (≥4 areas of challenge). All HCPs in this study will be OTs who are trained to assess individuals’ abilities or disabilities through the use of standardized testing and functional observation. As a result, the study protocol includes a condition that referral decisions for physician oversight or further testing are the purview of the HCP and their clinical judgment. This became the proxy gold standard for a positive screen in this research study.

Following the review of the results at each appointment, the HCP will provide patients with a handout that summarizes recommendations for supporting cognitive health. If the SCREEN identifies any *areas of challenge,* the patient will also receive a handout developed by BrainFx containing tailored strategies to strengthen brain health and manage deficits in those areas.

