#### Descriptive and Inferential Analysis

Descriptive data will be described using frequencies and percentiles and compared using the chi-square test or Fisher exact test as necessary. Continuous data will be analyzed for central tendency and variability; categorical data will be presented as proportions. Normality will be tested using the Shapiro-Wilk test, and nonparametric tests will be performed using the Mann-Whitney U test*.* Statistical significance will be considered at a *P* value of .05, with 90% CI provided where appropriate. We powered the exploratory analysis to validate the SCREEN using an estimated effect size of 12%, with the understanding that Canadian prevalence rates are not available [29], and determined that we needed at least 114 participants. For test-retest reliability, using 90% power and a 5% type 1 error rate, we will require a minimum of 58 test results.

MCI test outcome data will be coded into a binary format of *healthy* or *unhealthy* (where unhealthy indicates a positive result on the test, ie, 1 or more *areas of challenge* on the SCREEN results, or a score of ≤67/100 on the Qmci) to account for the difference in categorical versus continuous outcome variables. For this reason, sensitivity and specificity will be determined using cross-tabulation rather than using the area under the curve using receiver operating characteristic curves. A principal component analysis with varimax rotation will be used to better understand the derivation of components’ contribution to screen test outcomes and to explore the differences between a conventional MCI screen (Qmci) and one that is intended to be more ecologically valid by assessing functional impairment (SCREEN). Binary logistic regression will examine the effects of variables such as age, education, self-reported comfort with technology, anxiety before and after completing the MCI tests, and sleep levels on the results. The internal consistency of both the SCREEN and Qmci will be assessed using Cronbach α. Test-retest reliability, the ability of a measurement instrument to reproduce results on 2 or more occasions (ceteris paribus), will be assessed using an intraclass correlation coefficient [106].

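### Sensitivity pools every Qmci score of 67 or below, so it measures detection of any Qmci-defined impairment and may overstate sensitivity for MCI

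*Protocol article*

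**What the plan says.** The protocol article defines the reference-positive class twice, in the same way. Under Psychometric Evaluation, unhealthy "denotes SCREEN=1 or more areas of challenge and Qmci≤67". Under Descriptive and Inferential Analysis, the outcomes are coded in two classes, "where unhealthy indicates a positive result on the test, ie, 1 or more" areas of challenge on the SCREEN, "or a score of ≤67/100 on the Qmci". That section also says that accuracy will come from a cross-tabulation and not from an ROC analysis.

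The section on the Qmci Screen gives three thresholds. The first is the one used: "The overall cut-off score to distinguish normal cognition from MCI on the Qmci is ≤67". The other two separate scores "from cognitive impairment (MCI or dementia) ≤62, and dementia alone ≤54". The accuracy analysis does not use these lower thresholds.

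On who can enter, the Patients section admits "Patients 55 years and older with no history of diagnoses for MCI, dementia, or Alzheimer disease", and the exclusion list likewise names a diagnosis. The introduction (MCI Disorder) reports that "only 20%-50% of people with dementia are recognized and documented in primary care". Ethics and Consent provides for patients who may have a neurocognitive disease.

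On the target, the Methods paragraph of the abstract says the accuracy tests will judge SCREEN as a screening tool for MCI, and the Conclusions paragraph speaks of early detection of MCI. The Objective paragraph and the list of objectives are wider and refer to early signs of cognitive impairment.

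**The concern.** A patient scoring 40 on the Qmci and one scoring 66 count alike as reference positives. If the sample includes people in the dementia range, sensitivity is an average over two severities, and the cross-tabulation keeps nothing that would separate them.

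The article's own account of the constructs makes a difference between severities plausible. It describes dementia as involving loss of functional competence, and says that people with MCI generally keep both basic and complex daily activities. SCREEN is meant to test functional competence. The article also criticises existing screens for being weak on mild impairment, and a pooled sensitivity could hide that same weakness in SCREEN.

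The abstract says the results will help the developers decide whether controlled testing is warranted. For that decision they need to know whether SCREEN found mild impairment or mainly dementia-range impairment. Specificity is not affected, because it is computed among Qmci negatives.

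**Working it through.** **The plan's figure.** The article states no expected sensitivity. Its only related figure is the 114 participants based on 12%. A single-proportion precision formula reproduces it: n = z²p(1−p)/d² = 1.645² × 0.12 × 0.88 / 0.05² = 114.3. The 90% level is the one the plan names; the half-width of 0.05 is my assumption. A 95% interval with a half-width of 0.06 gives 112.7, so the derivation is not unique. If 12% is read as the rate of Qmci positives (also an assumption), 0.12 × 114 = 13.7, or about 14 reference positives.

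**Formula.** Let w be the share of reference positives scoring 54 or below, and let Se_MCI and Se_dem be SCREEN's sensitivity at 55-67 and at 54 or below. Then

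pooled sensitivity = (1 − w) × Se_MCI + w × Se_dem,

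and the shift against Se_MCI is w × (Se_dem − Se_MCI). None of the three inputs is in the documents, so every value below is assumed.

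| Se_MCI | Se_dem | w | Shift (points) |
|---|---|---|---|
| any | any | 0 | 0 |
| 0.80 | 0.80 | any | 0 |
| 0.70 | 0.60 | 0.20 | 0.20 × (−0.10) = −2.0 |
| 0.90 | 0.98 | 0.10 | 0.10 × 0.08 = +0.8 |
| 0.70 | 0.95 | 0.10 | 0.10 × 0.25 = +2.5 |
| 0.70 | 0.95 | 0.20 | 0.20 × 0.25 = +5.0 |
| 0.60 | 0.95 | 0.30 | 0.30 × 0.35 = +10.5 |

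**As counts out of 14.**
- If 1 to 3 positives are in the dementia range and SCREEN flags them all, a true 0.70 reads (13 × 0.70 + 1)/14 = 0.72 to (11 × 0.70 + 3)/14 = 0.76. A true 0.90 reads 0.91 to 0.92, a shift of +0.7 to +2.1 points.
- With 5 of 14 in the dementia range, Se_dem 0.95 and Se_MCI 0.60, the pooled figure is (5 × 0.95 + 9 × 0.60)/14 = 0.725, a shift of +12.5 points.
- With Se_MCI 0.50 instead, it is (5 × 0.95 + 9 × 0.50)/14 = 0.661, or +16.1 points. I leave this out of the range for the reason in the next step.

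**What the SCREEN rule implies.** A positive needs only one of seven activities at least 1 SD below the reference mean. With normal, independent scores, a person at the reference mean is flagged with probability 1 − (1 − 0.1587)^7 = 0.70. Simulation with a common correlation of 0.7 gives 0.39. A sensitivity of 0.50 in MCI would therefore be no better than the rate at which average people may be flagged. If people with MCI sit 0.75 SD below the mean and people with dementia 2 SD below, the simulated sensitivities are 0.706 and 0.973 at correlation 0.7, and 0.972 and 1.000 at correlation 0. At w = 0.20 the shifts are 0.20 × 0.267 = +5.3 points and 0.20 × 0.028 = +0.6 points.

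**Precision.** For a sensitivity of 0.80 on 14 positives, the 90% half-width is 1.645 × √(0.80 × 0.20/14) = 17.6 points. If 9 to 12 positives remain in the 55-67 band and sensitivity is 0.60, it is 1.645 × √(0.24/9) = 26.9 down to 1.645 × √(0.24/12) = 23.3 points. If SCREEN flags all k people at 54 or below, the exact 90% lower limit is 0.05^(1/k): 0.22 for k = 2 and 0.55 for k = 5.

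**The case against.** **The pooled class is defensible for a screen.** The threshold of 67 is the one the article gives for normal cognition versus MCI. A primary care patient with unrecognised dementia is properly a true positive in the population where SCREEN would be used, and part of the article words the aim as early signs of cognitive impairment. This stands, and it is why the pooled figure should remain the main result. It does not justify presenting that figure as accuracy for MCI, which is the target the abstract states for these tests.

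**A reader might infer that the sensitivity is inflated as a matter of fact.** The documents do not support that. The 20%-50% recognition figure describes people who have dementia; it is not a prevalence in this sample. Several features may keep dementia-range scores few: entry from age 55, a minimum level of schooling, repeat visits three months apart, and consent that asks participants to explain the study back. The Limitations section expects self-selection by people worried about their cognition, but also by people at ease with tablets. SCREEN's sensitivity by severity is unknown, and the permissive one-of-seven rule limits how far dementia cases can raise the figure.

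**A reader might also infer that Qmci 55-67 should become the headline figure because it isolates MCI.** It does not. By the article's own thresholds, scores of 62 or below may be MCI or dementia, so 55-62 remains mixed. With about 9 to 12 positives the estimate would also be very imprecise.

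**Interval width and level of detail.** The interval on 14 positives is wider than any shift shown above, but width does not remove a mismatch between the label and the quantity, and more patients would not correct it. A breakdown by band could be left to a fuller plan. The definition of the class and the choice of a single cross-tabulation, however, are fixed in the article.

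**Conclusion.** The concern holds as a mismatch between target and analysis. The planned sensitivity is for any Qmci-defined impairment, including scores of 54 or below, while the stated target is MCI and only diagnosed dementia is excluded. It may overstate sensitivity for MCI, on two conditions: some participants score 54 or below, and SCREEN flags them more readily than those at 55-67. The second is plausible from the article's description of the constructs, but it is not shown.

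The size cannot be derived from the documents. Under the assumed inputs it runs from about zero, or slightly negative, to about +10 points or slightly more. It is small, about 1 to 2 points, if SCREEN's sensitivity for MCI is already near 0.90. A Qmci score in either band is a screen result and not a diagnosis, so no banding can turn the figure into a true sensitivity for MCI.

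**What to change.** In Descriptive and Inferential Analysis:

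- Keep the pooled cross-tabulation at 67 or below as the main result, and label it as sensitivity for any Qmci-defined impairment.
- Beside it, report the proportion flagged by SCREEN, with numerator, denominator and confidence interval, for Qmci 55-67 and for 54 or below. An exact interval suits these counts.
- Base any statement about early MCI on the 55-67 row.
- Add a note that the bands are screen results and that 55-62 can still include dementia by the article's own thresholds.

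This needs no new data, because the Qmci is scored out of 100 at every visit. The cost is one extra table with small denominators and wide intervals. The row for 54 or below may hold only a few people, or none.

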#### The SCREEN

The SCREEN (version 0.5, beta) will be administered on a tablet (ASUS ZENPAD 10.1“ WXGA IPS Display, 1920×1200), powered by a quad-core 1.5 GHz, 64-bit MediaTek MTK 8163A processor with 2 GB RAM and 16 GB storage. The tablet comes with a tablet stand for optional use and a dedicated stylus that is recommended for completion of a subset of activities. At the start of the study, HCPs will be provided with identical tablets, preloaded with the BrainFx app software for use for the duration of the study.

Using a standardized administration protocol developed by BrainFx, the HCP will instruct the patient to use either their finger or the provided stylus to complete the SCREEN. Following acclimation to the tablet, the patient will be required to complete a short survey to collect demographic information (eg, age, the highest level of education attained) and any history of pre-existing conditions and questions about the patients’ state of well-being at the time of testing (eg, self-reported concerns about their thinking, mood, hours slept, and pain). The questionnaire will be immediately followed by 7 activities that are modeled after everyday real-world actions purported to evaluate functional competence related to a variety of cognitive domains, including abstract reasoning, divided attention, or visual-spatial abilities (refer to Table 1 for a detailed description of the activities). Tasks will be timed and digitally scored, and an activity score for each activity will be generated based on a combination of the patients’ accuracy (ie, number of correct responses) and processing speed (ie, speed of completion). The relative weight that accuracy and processing speed contribute to the activity score is proprietary to BrainFx and is the same for each of the 7 activities.

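### The reason given for reducing both screens to binary codes and avoiding ROC does not fit the protocol's own description of the scores, and no score-level SCREEN–Qmci association is named

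*Protocol article*

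**What the plan says.** The first objective of the study is a psychometric evaluation of the SCREEN. Under Descriptive and Inferential Analysis, each test result is coded as healthy or unhealthy (unhealthy: at least one area of challenge on the SCREEN, or a Qmci of 67 or less). The reason given is "to account for the difference in categorical versus continuous outcome variables", and the next sentence uses it to choose cross-tabulation over the area under an ROC curve.

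The same section names binary logistic regression for covariates such as age, education, comfort with technology, anxiety and sleep. It also names a varimax principal component analysis, Cronbach α for both screens, and an intraclass correlation for test-retest reliability.

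The scales are described under Measures:
- **SCREEN:** "an activity score for each activity will be generated based on a combination of" accuracy and processing speed. The report shows that score, and a task is flagged when the score lies 1 SD or more below the reference mean.
- **Qmci:** it "is scored by hand out of 100 points".

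Under Psychometric Evaluation the protocol also grades the SCREEN by the number of areas of challenge: zero, up to three, or four and more.

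**The concern.** The categorical form of the SCREEN is imposed by a cut and is not inherent in the instrument. A difference in scale would not rule out ROC in any case: ROC needs a binary reference, which Qmci ≤67 supplies, and an index test that is at least ordinal, which the count of areas of challenge supplies.

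Because the reason is mistaken, what follows from it deserves a second look. The article names no correlation, regression or other score-level estimate of how the SCREEN and the Qmci move together, although such an estimate is ordinary evidence of convergent validity under the first objective. The covariate question is also put only to dichotomies. Both choices cost precision in a study of modest size.

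**Working it through.** **The plan's own figure.** The article says it "determined that we needed at least 114 participants", "using an estimated effect size of 12" percent. Neither the kind of effect, the test nor the power is given, so 114 cannot be tied to one formula. One variant comes close: a single proportion of 0.12 with a 90% CI and an assumed half-width of 5 points gives 1.645² × 0.12 × 0.88 / 0.05² = 114.3. Other variants also land near 114. Below, 114 serves only as the sample size.

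**Assumptions.** Normal underlying scores; Qmci-positive rates of 12%, 30% and 50%; weak-effect approximation for efficiency. The article gives none of these as expected rates of a positive screen.

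**SCREEN-positive rate.** One task cut at −1 SD flags 15.9% of a normal reference population. With seven independent tasks, at least one flag occurs in 1 − 0.841⁷ = 70%. With an inter-task correlation of 0.5 the rate is 47%, and with 0.7 it is 39%.

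**Information kept by one split** at positive rate p is φ(z_p)² / [p(1 − p)], where φ is the normal density:

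| p | kept | equivalent of 114 patients | lost |
|---|---|---|---|
| 12% | 0.2000² / 0.1056 = 0.379 | 43 | 62% |
| 20% | 0.490 | 56 | 51% |
| 30% | 0.576 | 66 | 42% |
| 50% | 0.637 | 73 | 36% |

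This is the loss for covariate effects on one screen. At SCREEN-positive rates of 39–70%, 0.58–0.64 is kept.

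**Information kept on the association when both are split** is the product of the two efficiencies:
- Qmci 12%, SCREEN 70%: 0.379 × 0.575 = 0.218, so 78% is lost.
- Qmci 30%, SCREEN 70%: 0.576 × 0.575 = 0.331, so 67% is lost.
- Both at 50%: 0.637² = 0.41, so 59% is lost.

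**The same in terms of power** (n = 114, two-sided 0.05, assumed true correlation 0.30):
- From scores: atanh(0.30) × √111 − 1.96 = 1.30, power 90%.
- From the 2×2 table, with power Φ(phi × √114 − 1.96):

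| Qmci-positive | SCREEN-positive | phi | power |
|---|---|---|---|
| 12% | 70% | 0.126 | 27% |
| 12% | 50% | 0.146 | 35% |
| 30% | 50% | 0.184 | 50% |
| 50% | 50% | 0.194 | 54% |

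For an observed correlation of 0.50, the 90% CI (the level the article uses) would be tanh(0.549 ± 1.645/√111) = 0.37 to 0.61.

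**The case against.** The case on the other side has real weight.

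- **Sensitivity and specificity need a cut-off.** The stated aim is to compare sensitivity, specificity and reliability, so a 2×2 table is legitimate and should stay. A correlation answers a different question. Its narrower interval does not show that the planned estimates are poor.
- **The SCREEN has no described total score.** What the user reads is largely a set of per-task flags, so calling its outcome categorical is loose but not baseless. This stands in part. The activity scores and the count still exist, but nothing says that the seven scores share a scale, so a plain mean cannot be taken for granted.
- **A journal article condenses.** Supplementary correlations could sit in a fuller document. That would explain a missing analysis. It does not explain a reason that is stated in the article and conflicts with the article's own account of the measures.
- **Logistic regression on the study's own outcome is defensible.** This also stands, so the logistic models can be kept beside score-based ones.

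A reader might go further and infer that the plan discards most of the information in 114 patients, or that 114 act like 43. The document does not support that. The principal component analysis, Cronbach α and the intraclass correlation are not tied to the binary codes. The figure of 43 needs a 12% positive rate, whereas the article attaches 12% to an undefined effect size, says Canadian prevalence is unavailable, cites MCI in up to 42% of people over 60, and expects people with cognitive concerns to self-select. For covariates, the loss exceeds half only when the positive rate is below about 20%.

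Nor is it right that the screens are never related: the 2×2 table relates their dichotomies, and the principal component analysis is meant to explore how they differ.

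**Conclusion.** The point holds in a limited form. The stated reason for binary coding, and for setting ROC aside, is unsound on the protocol's own description of the two instruments. Besides an exploratory principal component analysis, which gives no estimate or interval for how the scores move together, the 2×2 table is the only direct SCREEN–Qmci comparison named. Covariates are examined only on dichotomies.

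The cost is about 59–78% of the information on the association between the screens, and about 36–62% on covariate effects. These ranges rest on normality, weak effects and assumed positive rates (12–50% for a single split or for the Qmci, up to 70% for the SCREEN). The power figures also assume a true correlation of 0.30. The planned sensitivity and specificity are not invalidated. This is an inexpensive gain in precision and in validity evidence.

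**What to change.** 1. Keep the 2×2 table, and delete the scale difference as its justification. It is enough to say that sensitivity and specificity are wanted at the stated cut-offs.
2. Add, at the first visit, Spearman correlations with confidence intervals between the Qmci total and the count of areas of challenge, and between the Qmci total and each activity score. Use a mean of the seven scores only if they are confirmed to share a scale or are standardised first.
3. Add an ROC curve and AUC for the count against Qmci ≤67. If 12% were positive, there would be only about 114 × 0.12 ≈ 14 positive patients, so the AUC would itself be imprecise and should carry its interval.
4. Model covariates on the Qmci total and on the SCREEN count or scores, and report the logistic models alongside.

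The Qmci total and the SCREEN report with its activity scores are already obtained at each visit, so no new data collection is needed. The cost is a few more analyses and the need to fix the SCREEN summary score before the data are analysed.
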